# Phase II, multi-center, open-label, single-arm clinical trial evaluating the efficacy and safety of Mycophenolate Mofetil in patients with high-grade locally advanced or metastatic osteosarcoma (ESMMO): rationale and design of the ESMMO trial

**DOI:** 10.1186/s12885-020-06751-2

**Published:** 2020-03-30

**Keywords:** Osteosarcoma, Mycophenolate mofetil, Phase II, Clinical trial, Cancer

## Abstract

**Background:**

Clinical outcomes of patients with osteosarcoma remain unsatisfactory, with little improvement in a 5-year overall survival over the past three decades. There is a substantial need for further research and development to identify and develop more efficacious agents/regimens in order to improve clinical outcomes of patients for whom the prognosis is unfavorable. Recently, mycophenolate mofetil, a prodrug of mycophenolic acid, has been found to have anticancer activity against osteosarcoma in both in vitro and animal experiments, so that further investigation in humans is warranted.

**Methods:**

A total of 27 patients with high-grade locally advanced or metastatic osteosarcoma will be enrolled into this phase II, multi-center, open-label, single-arm, two-stage clinical trial. The main objectives of this study are to determine the efficacy and safety of mycophenolate mofetil in the patients. The primary endpoint is progression-free survival at 16 weeks; the secondary endpoints include progression-free survival, overall survival, overall response rate, safety parameters, pharmacokinetic parameters, biomarkers, pain score, and quality of life. Mycophenolate mofetil at the initial dose of 5 g/day or lower will be administered for 4 cycles (28 days/cycle) or until disease progression or unacceptable toxicity. The dose of mycophenolate mofetil may be reduced by 1–2 g/day or withheld for some Grade 3 or Grade 4 toxicities whenever clinically needed. The duration of study participation is approximately 4–5 months, with a minimum of 12 study visits. If mycophenolate mofetil proves beneficial to some patients, as evidenced by stable disease or partial response at 16 weeks, administration of mycophenolate mofetil will continue in the extension period.

**Discussion:**

This trial is the first step in the translation of therapeutic potential of mycophenolate mofetil emerging from in vitro and animal studies into the clinical domain. It is designed to assess the efficacy and safety of mycophenolate mofetil in patients with high-grade locally advanced or metastatic osteosarcoma. The results will provide important information about whether or not mycophenolate mofetil is worth further development.

**Trial registration:**

This trial was prospectively registered on Thai Clinical Trials Registry (registration number: TCTR20190701001). The posted information will be updated as needed to reflect protocol amendments and study progress.

## Background

Osteosarcoma is one of the most common primary malignant tumors of the bone in adolescents and young adults, with the incidence of approximately 2–4 per million worldwide [1–4]. The substantial advance in the treatment of osteosarcoma occurs in the 1970s and 1980s, when chemotherapy was shown to significantly improve the survival outcome of the patients with localized disease undergoing surgical resection [5, 6]. However, little further progress has been observed since then, with a 5-year overall survival remaining at approximately 70 and 30% in patients with localized and metastatic disease at diagnosis, respectively [7, 8]. At present, the combination of surgical resection and systemic chemotherapy with, at least, three active drugs (i.e., doxorubicin, cisplatin, and high-dose methotrexate) remains the standard treatment for patients with osteosarcoma [9–11].

Mycophenolate mofetil is an immunosuppressive agent currently being used for the prophylaxis of organ rejection following transplantation [12, 13]. It is a prodrug of mycophenolic acid (MPA), a potent inhibitor of inosine monophosphate dehydrogenase (IMPDH) [14, 15]. In some cancer in which IMPDH is upregulated, MPA may possess anti-cancer activity [16]. In 2010, Fellenberg et al. reported the observed overexpression of IMPDH in metastatic and chemo-resistant osteosarcoma cell lines, and pharmacological inhibition of IMPDH could result in a reduction of cell viability and cell proliferation [17]. A recent in vitro study has revealed the anticancer activity of MPA against osteosarcoma cell lines, with the half maximal inhibitory concentration (IC_50_) of 0.46–7.30 μM across all tested cell lines [18]. The in vivo experiment has shown the inhibition of tumor growth and lung metastasis of osteosarcoma in mice treated with mycophenolate mofetil [18]. As a result, mycophenolate mofetil has been recently proposed to be a promising new drug candidate for the treatment of osteosarcoma [19].

With the therapeutic potential of mycophenolate mofetil against osteosarcoma in in vitro and animal experiments, further investigation in humans is warranted. Since mycophenolate mofetil has been widely used in humans for decades, particularly in organ transplant recipients, with a satisfactory safety profile, a phase I clinical trial aimed solely at determining the safety and tolerability of the drug may not be required. A single-arm phase II clinical trial is considered to be the first step in the translation of therapeutic potential of mycophenolate mofetil emerging from in vitro and animal studies into the clinical domain before the drug development process can move forward to a randomized-controlled, phase III clinical trial. The efficacy and safety of mycophenolate mofetil will be first assessed in patients with high-grade locally advanced or metastatic osteosarcoma in this proposed phase II clinical trial.

## Methods/design

### Study objectives

The primary objective of this study is to assess the anticancer activity of mycophenolate mofetil in patients with high-grade locally advanced or metastatic osteosarcoma, and the secondary objective is to assess the safety and tolerability of the drug. The present study also aims to explore the pharmacokinetics of mycophenolate mofetil, biomarkers, and the quality of life in patients with high-grade locally advanced or metastatic osteosarcoma.

### Study design

This prospective study is an open-label, single-arm, two-stage phase II clinical trial of mycophenolate mofetil orally administered at the dose of 5 g/day (or lower) for 4 cycles (28 days/cycle) or until disease progression or unacceptable toxicity. This two-stage phase II clinical trial plans to involve a total of 27 adolescent and adult patients with high-grade locally advanced or metastatic osteosarcoma. In Stage 1, 19 patients will be enrolled, and the trial will continue to Stage 2 and enroll additional 8 patients only if at least 3 patients in Stage 1 achieve the primary endpoint.

### Study setting

This trial will be conducted at multiple centers in Thailand, where the Faculty of Medicine, Chiang Mai University is the primary study site.

### Study endpoints

The primary endpoint of this trial is progression-free survival (PFS) (or disease control rate (DCR)) at 16 weeks. The secondary endpoints include PFS, overall survival (OS), overall response rate (ORR) (based on the RECIST criteria version 1.1) [20, 21], safety parameters (according to the Common Terminology Criteria for Adverse Events (CTCAE) version 5.0), pharmacokinetic (PK) parameters (i.e., plasma levels of MPA and its metabolites), biomarkers (consisting of lactate dehydrogenase and circulating tumor cells), pain score (using the Thai version of Brief Pain Inventory (BPI) [22]), and quality of life (using the EORTC QLQ-C30 questionnaire version 3.0 and the EORTC QLQ-LC13 questionnaire).

### Inclusion criteria

Evidence of histologically documented diagnosis of high-grade locally advanced or metastatic osteosarcoma, not amendable to surgery, radiation, or combined modality therapy with curative intent;Measurable disease, determined within 28 days prior to enrollment;Evidence of disease progression after treatment with, at least, one standard chemotherapy regimen for osteosarcoma or evidence of patient refusal for any further treatment with standard chemotherapy regimens for advanced disease;ECOG performance status of ≤2, with an estimated life expectancy of > 3 months;Age ≥ 13 years at the date of enrollment;Adequate organ function, determined by laboratory tests within 14 days prior to enrollment; andInformed consent obtained (or assent, when applicable).

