### Exclusion criteria

History of another malignancy within 5 years prior to study entry, except curatively treated non-melanotic skin cancer or other solid tumors curatively treated with no evidence of disease for > 3 years;Current treatment with another investigational agent and/or systemic anticancer therapy within 4 weeks prior to enrollment;Surgery and/or radiotherapy for curative intent within 1 month prior to enrollment;History of allergic reactions attributed to mycophenolate mofetil, MPA, allopurinol (including the presence of HLA-B*5801, indicating an increased risk of severe cutaneous adverse reactions to allopurinol), ivermectin, trimethoprim-sulfamethoxazole (or sulfa drugs), acyclovir or any ingredients of the drugs;History of severe or uncontrolled medical conditions or laboratory abnormality;Impaired renal function (with creatinine clearance of < 45 mL/min);Known or suspected pregnancy or breastfeeding;Any other conditions in which mycophenolate mofetil, allopurinol, ivermectin, trimethoprim-sulfamethoxazole, or acyclovir is contradicted;Unable to swallow oral medications;Major surgery within 4 weeks prior to study entry; orSignificantly altered mental status.

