### Sample size determination

The sample size was calculated according to the Simon’s minimax two-stage design, with PFS at 16 weeks as the primary endpoint. PFS is dichotomized according to whether PFS is ≤16 weeks (defined as disease control failure (DCF)) or > 16 weeks (defined as disease control success (DCS)). Therefore, treatment with mycophenolate mofetil will be considered successful if the 16-week radiological evaluation indicates stable disease, partial response, or complete response, as defined by the RECIST criteria version 1.1. Patients alive after 16 weeks without signs of progression will be regarded as DCS.

The sample size was calculated under a hypothesis of interest in which DCS at 16 weeks is ≥32% (*p*_1_ = 0.32, the minimal proportion of successes that makes the experimental treatment worth further studies) and a null hypothesis in which mycophenolate mofetil reaches a DCS at 16 weeks < 12% (*p*_0_ = 0.12, the proportion of successes that implies no clinically worthwhile activity of the experimental treatment). Setting *α* = 0.10 (where *α* represents the probability of failing to reject a treatment with response probability ≤*p*_0_) and *β* = 0.10 (where *β* represents the probability of rejecting a treatment with response rate ≥ *p*_1_), this condition requires 19 patients to be enrolled in Stage 1. Recruitment will continue to reach a total of 27 patients if the number of DCS among the first 19 patients is at least 3; otherwise, the trial will be stopped for inefficacy after analysis of 19 patients. As per the study protocol, mycophenolate mofetil will be deemed promising and worth further studies if at least 6 DCS is observed at the end of the study.

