### Justification for the study design and study endpoints

In phase II osteosarcoma trials, a single-arm design may be preferred to a randomized-controlled design owing to the fact that osteosarcoma is a rare disease, with a limited number of patients available to be enrolled in early-phase clinical trials with a specific and strict set of eligibility criteria [38]. Based on a systematic review of past experience, most phase II osteosarcoma trials are conducted using a single-arm, two-stage design [39]. A single-arm design is considered appropriate for the evaluation of monotherapy when a well-defined historical control database is available, while a key limitation of this approach is that any changes in patient management over time may shift the expected outcome (e.g., PFS) above the historical benchmark [40]. In the case of osteosarcoma, the standard treatment for newly diagnosed and recurrent disease has not substantially been changed over the past three decades, so that the historical benchmark for the outcome of patients could be reliably used [41].

One of the major characteristics of osteosarcoma is that tumor volume shrinkage, determined by radiographic imaging, may not reflect the efficacy of an anticancer agent at the cellular level since tumor tissue is customarily substituted by the calcified matrix [42]. Even if the treatment is effective, the calcified matrix may still prevent volume reduction of the tumor [43]. Hence, objective radiographic responses in osteosarcoma are rarely observed, even with proven complete necrosis in the tumor after neoadjuvant chemotherapy [44]. In addition, the chance of spontaneous stability in advanced osteosarcoma is estimated to be extremely low [45]. Therefore, it may be reasonable to regard ‘stable disease’, rather than only ‘complete response’ and ‘partial response’, at a pre-specified, justified period as an appropriate surrogate endpoint in this specific group of population [39]. This is in agreement with the recent analysis of seven phase II osteosarcoma trials, where PFS > 4 months (defined as DCS) is used as a primary endpoint [44]. It is, thus, reasonable to consider PFS at 16 weeks (or disease stabilization at 16 weeks) as a success in this ESMMO trial setting where a decrease of tumor volume is not expected.

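### The progression criterion has no time limit and no tie to the latest therapy, so a patient left stable by a later, completed line can enter and count as a mycophenolate success

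*Protocol article*

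**What the plan says.** In the protocol article, Inclusion criteria, one item offers two routes into the trial. The first is "Evidence of disease progression after treatment with, at least, one standard chemotherapy regimen for osteosarcoma". The second, in the same sentence, is "or evidence of patient refusal for any further treatment with standard chemotherapy regimens for advanced disease". Neither carries a date. Other items in that list do: "Measurable disease, determined within 28 days prior to enrollment", and laboratory tests within 14 days.

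The Exclusion criteria bar "Current treatment with another investigational agent and/or systemic anticancer therapy within 4 weeks prior to enrollment".

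Under Sample size determination, "treatment with mycophenolate mofetil will be considered successful if the 16-week radiological evaluation indicates stable disease, partial response, or complete response" at that time point, and "Patients alive after 16 weeks without signs of progression will be regarded as DCS". The notes to Table 3 place tumour imaging at baseline and at 8 and 16 weeks (each ± 1 week) after the drug is started.

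The null rate is p0 = 12%. Sample size justification takes it from patients with recurrent or refractory osteosarcoma in seven phase II trials (95% CI 6% to 19%). Counting stable disease as success is defended under Justification for the study design and study endpoints on the ground that "the chance of spontaneous stability in advanced osteosarcoma is estimated to be extremely low".

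**The concern.** The endpoint rewards absence of growth over 16 weeks. In a trial without a control arm, that supports a drug effect only if the disease would otherwise have been growing. The progression route does not secure this. It is met by any progression after any one standard regimen, however long ago and whatever was given since.

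The argument about spontaneous stability does not fill the gap, because stability left behind by an earlier effective treatment is not spontaneous. If enough such patients enter, the success rate expected under an inactive drug exceeds that of patients who are progressing at entry, and the earlier treatment's effect is credited to mycophenolate. Sample size justification itself notes that setting p0 too low raises the type I error. What is at stake is the reliability of the decision to develop the drug further.

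**Working it through.** **1. Can such a patient enter?** Take a patient who progressed after first-line chemotherapy, reached stable disease or partial response on a second line, finished it 5 weeks ago and has residual lesions.

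- Progression after at least one standard regimen: met by the first-line progression.
- Measurable disease within 28 days: met. It shows that lesions exist, not that they are growing.
- No systemic anticancer therapy within 4 weeks: met. A patient still receiving the second line would be excluded.
- Endpoint: the comparison starts from a new baseline scan, so unchanged lesions at 16 weeks are a success.

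No other listed criterion asks about current growth.

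**2. The plan's own design.** Inputs from Sample size determination: p0 = 0.12, p1 = 0.32, α = β = 0.10; continue if at least 3 of 19 succeed; promising if at least 6 of 27 succeed. With X1 ~ Bin(19, p) and X2 ~ Bin(8, p),

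P(promising | p) = Σ over x from 3 to 19 of P(X1 = x) · P(X2 ≥ 6 − x).

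This gives 0.0936 at p = 0.12 and 0.9000 at p = 0.32. A search for the smallest total sample size meeting both error limits returns the same design (19/27, cut-offs 3 and 6). The stated design is correct. It has little slack: P(promising) reaches 0.10 at p of about 0.122.

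**3. Sensitivity to the patients admitted.** Let f be the share not progressing at entry and q their 16-week stability without drug effect; the rest succeed at 12%. Then p = 0.12(1 − f) + q·f.

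The documents give neither f nor q, so all values below are assumptions. For a low q, I use the only time-to-progression figure in the article, a median of about 1.8 months in inoperable disease (Sample size justification). With exponential times and 16 weeks = 112/30.44 = 3.68 months, q = 2^(−3.68/1.8) ≈ 0.24. That median is not specific to patients stable after therapy. The values 0.40 and 0.50 are illustrative.

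Examples: f = 0.10, q = 0.50 gives p = 0.108 + 0.050 = 0.158; f = 0.15, q = 0.24 gives p = 0.102 + 0.036 = 0.138.

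| f | q = 0.24 | q = 0.40 | q = 0.50 |
|---|---|---|---|
| 0 | 9.4% | 9.4% | 9.4% |
| 1/27 (one patient on average) | 10.7% | 12.7% | 14.0% |
| 10% | 13.3% | 19.5% | 24.0% |
| 15% | 15.5% | 25.9% | 33.3% |

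Entries are the probability of declaring an inactive drug promising. The rate rises whenever q exceeds 12%; if q is 12% or less, there is no inflation.

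**The case against.** The strongest reply has four parts.

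- **Condensed text.** This is a journal article, and in a trial of advanced, incurable disease the natural reading may be that the current disease has progressed. The full protocol may say so. That is possible, but the article's list does give windows for measurable disease and laboratory tests. As written, the progression rule is complete and is satisfied by old progression.
- **Narrow case.** A reader might infer that patients stable while on a later line qualify. They do not, because the 4-week exclusion bars ongoing or recent systemic therapy. What stands is the patient whose later line ended more than 4 weeks earlier.
- **The null rate.** A reader might infer that 12% is shown to be too low. It is not. The article does not say whether the seven source trials required progression after the latest therapy. If they admitted a similar share of non-progressing patients, 12% already reflects them and there is no mismatch. The label recurrent or refractory does not decide the matter.
- **Size.** It is tempting to quote only the 26% to 33% for f = 15% and q = 0.40 to 0.50. Those are high-end assumptions. With one such patient in 27 and q = 0.24, the rate is 10.7%, close to the planned 10%.

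A further objection is that mending the progression route alone would achieve little, since the refusal route requires no progression at all. That is correct and changes the fix.

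**Conclusion.** The gap in the criterion is real: progression need be neither recent nor related to the latest therapy. A patient stable or responding after a completed later line can therefore be a disease-control success with no contribution from mycophenolate. The sample size, stage rules and attained error rates are correct for p0 = 12%.

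The effect on the false-positive rate is conditional. Against 9.4% as designed, it is about 11% to 14% with one such patient in 27, 13% to 24% at 10% of entrants, and 15.5% to 33% at 15%. These ranges assume q of 0.24 to 0.50, a 12% success rate in everyone else, and a source population for p0 that did not already contain such patients. The documents establish none of the three. The trial can run as designed, but the wording should be tightened because its go decision depends on the disease growing at entry.

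**What to change.** Require radiological progression documented on or after the most recent systemic therapy, within a look-back window that the sponsor states and justifies; the documents support no particular length. The screening scan compared with an earlier one could serve as evidence. If the full protocol already says this, the article's wording should be brought into line with it.

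Apply the same requirement to the refusal route, otherwise non-progressing patients still enter by it. If that route is kept as it is, record progression status at entry and report 16-week disease control separately by that status.

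The cost is a short rewording of one inclusion item. A patient stable after a later line, or one refusing further chemotherapy without progression, would wait until progression is shown, so accrual may slow slightly. The figures 19 and 27 and the cut-offs 3 and 6 do not change.

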### Exclusion criteria

History of another malignancy within 5 years prior to study entry, except curatively treated non-melanotic skin cancer or other solid tumors curatively treated with no evidence of disease for > 3 years;Current treatment with another investigational agent and/or systemic anticancer therapy within 4 weeks prior to enrollment;Surgery and/or radiotherapy for curative intent within 1 month prior to enrollment;History of allergic reactions attributed to mycophenolate mofetil, MPA, allopurinol (including the presence of HLA-B*5801, indicating an increased risk of severe cutaneous adverse reactions to allopurinol), ivermectin, trimethoprim-sulfamethoxazole (or sulfa drugs), acyclovir or any ingredients of the drugs;History of severe or uncontrolled medical conditions or laboratory abnormality;Impaired renal function (with creatinine clearance of < 45 mL/min);Known or suspected pregnancy or breastfeeding;Any other conditions in which mycophenolate mofetil, allopurinol, ivermectin, trimethoprim-sulfamethoxazole, or acyclovir is contradicted;Unable to swallow oral medications;Major surgery within 4 weeks prior to study entry; orSignificantly altered mental status.

### Withdrawal criteria

More than 4 weeks of study drug interruption due to toxicity;Disease progression or any significant deterioration in the health of the patient;Unacceptable toxicity;Occurrence of another illness which precludes further participation in this trial;Significant protocol noncompliance;Development of an illness or situation which would affect assessments of clinical status and study endpoints to a significant degree;Pregnancy;Patient lost to follow-up; orWithdrawal of informed consent.

Patients who withdraw or are withdrawn prematurely will be replaced only if they discontinue during the first four weeks due to reasons other than toxicity.

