### Stopping rules

In serious diseases (like high-grade locally advanced or metastatic osteosarcoma), the trial may need to stop prematurely if there is evidence of inefficacy [32]. Thus, this two-stage phase II clinical trial with a futility stopping based on Simon minimax criterion will be prematurely stopped if there is fewer than 3 DCS among the first 19 patients treated with mycophenolate mofetil.

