### Statistical analysis plan

All patients who receive at least one dose of mycophenolate mofetil will be included in an intention-to-treat analysis. Patients’ baseline demographics will be summarized using descriptive statistics. Study drug administration will be described in terms of the total number of cycles (or days) administered, the median (range) of cycles (or days) administered, dose intensity, and reasons for deviations from planned therapy. Adverse events will be collected after the patient has taken the first dose of mycophenolate mofetil.

The PFS at 16 weeks or DCR (the primary endpoint) will be measured as a binary variable: DCS or DCF. The PFS and OS will be summarized using the Kaplan-Meier method and displayed graphically as appropriate. For patients lost to follow-up, they will be censored at the date of the last follow-up visit. Median PFS and OS (and their corresponding 95% confidence intervals) will also be provided.

All statistical analysis will be executed using IBM SPSS Statistics for Windows, version 22.0, with a *p* value of less than 0.05 considered to indicate statistical significance. It is possible that the decision rule of this single-arm, two-stage phase II clinical trial may need to be adapted from the original plan [33]. If the attained sample size at the end of this study is different from the one that is initially planned due to any reason, a statistical testing will be conducted by calculating the *p* value with the sample size at the stopping stage conditioned on the observed value [34, 35]. The Jennison-Turnbull confidence interval may be used by treating the observed sample size at the stopping stage like the planned sample size [36].

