### Sample size justification

In this trial, the sample size determination is based on the rigorous evidence available to date so as to minimize the false positive rate owing to a single-arm design [53]. An under-estimation of *p*_0_ induces an increased type I error, while an over-estimation of *p*_1_ implies a loss of power [54]. In the retrospective analysis of the outcome of patients with recurrent/refractory osteosarcoma in seven phase II clinical trials conducted between 1997 and 2007, the DCS at 4 months is 12% (95% CI: 6 to 19%) [44]. The mean DCS probability of 12% is, thus, chosen to be the baseline response rate expected to be observed should mycophenolate mofetil be ineffective in this trial (*p*_0_ = 0.12). The effect size (*p*_1_-*p*_0_) that the experimental drug would still be of interest for further development is set at 20% (*p*_1_ = 0.32) [55]. In inoperable osteosarcoma settings, a median time to progress is around 1.8 months, with a median survival of around 6 months and 2-year survival of < 2% [45, 56, 57]. Therefore, the proportion of DCS of 32% can be considered appropriate to reflect the efficacy of mycophenolate mofetil whether or not it is worth further development [58].

In this trial, the minimax design is chosen to minimize the maximum sample size under the null hypothesis [55]. This is because the difference in expected sample sizes in this scenario is trivial as well as the patient accrual rate may be low. Furthermore, patients with high-grade locally advanced or metastatic osteosarcoma may be heterogeneous, so it is reasonable to assume that the patients entering early in the trial may not be representative of eligible population [55]. A small first stage may not be desirable, and the minimax design is preferable to the optimal design accordingly.

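### The four-week replacement rule covers early disease failures, contradicts the treated-patient counts, and can lift the type I error above 0.10 if those failures do not fill places in the 19 and 27

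*Protocol article*

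**What the plan says.** All references are to the protocol article.

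- **Withdrawal criteria.** One listed reason is "Disease progression or any significant deterioration in the health of the patient". The closing sentence says that withdrawn patients "will be replaced only if they discontinue during the first four weeks due to reasons other than toxicity". Toxicity is the only exception. Death is not named in the list.
- **Sample size determination.** PFS of 16 weeks or less is a disease control failure (DCF); longer PFS is a success (DCS). The design has 19 patients in stage 1, continues with at least 3 DCS, and calls the drug promising with at least 6 DCS among 27.
- **Stopping rules.** The trial stops early with "fewer than 3 DCS among the first 19 patients treated with mycophenolate mofetil".
- **Statistical analysis plan.** "All patients who receive at least one dose of mycophenolate mofetil will be included in an intention-to-treat analysis". If the attained sample size differs from plan for any reason, a p value is to be calculated at the attained size.

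**The concern.** Read as written, the replacement sentence takes in patients whose primary outcome is already known to be a failure. Progression and deterioration are not toxicity, so a dosed patient who leaves for either reason in the first four weeks is replaced.

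Three other statements do not fit with that. The stage 1 rule counts treated patients, the analysis set keeps everyone with one dose, and the decision rule fixes the totals at 19 and 27. Once dosed failures are replaced, it is unclear which patients make up the 19 and the 27.

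The direction of any bias is known. If certain failures give up their places to new patients, an inactive drug shows a higher success rate among those counted, and the fixed cut-offs are met too often. A single-arm trial has no control group to absorb this, and Sample size justification gives limiting false positives as an aim of the design.

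**Working it through.** **Inputs.** p0 = 0.12, p1 = 0.32, α = β = 0.10, n1 = 19, N = 27, cut-offs 3 and 6 (Sample size determination and Sample size justification). The share f of dosed patients who fail from disease in weeks 1 to 4 and are replaced is not given, so it is an assumption shown over a range. The 12% is taken as the rate among all dosed patients.

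**Step 1: reproduce the design.** "The sample size was calculated according to the Simon’s minimax two-stage design". The chance of declaring the drug promising is

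P(p) = Σ over x ≥ 3 of Bin(x; 19, p) × P[Bin(8, p) ≥ 6 − x].

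At p = 0.12:

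| Stage 1 DCS | Probability | Chance of reaching 6 | Product |
|---|---|---|---|
| 3 | 0.217 | 0.061 | 0.0132 |
| 4 | 0.118 | 0.248 | 0.0293 |
| 5 | 0.048 | 0.640 | 0.0309 |
| 6 or more | 0.0202 | 1 | 0.0202 |

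The sum is 0.0936. At p = 0.32, P = 0.900. The chance of a futility stop under the null is 0.597. A search over designs returns the stated 19/27 with these cut-offs as the minimax solution. The slack below 0.10 is only 0.0064.

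**Step 2: replaced failures leave both counts (reading A).** Only patients who are not early failures are counted, so the null rate becomes p0/(1 − f). For f = 10% it is 0.12/0.90 = 0.133, and the four products become 0.0184 + 0.0415 + 0.0451 + 0.0324 = 0.137.

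**Step 3: stage 1 counts the first 19 treated, as Stopping rules says, and accrual then runs to 27 non-replaced patients (reading B).** Let e be the early failures among the first 19. The second stage then has 8 + e patients, each with success rate 0.12/(1 − f):

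P = Σ over x ≥ 3 of Bin(x; 19, 0.12) × Σ over e of Bin(e; 19 − x, f/0.88) × P[Bin(8 + e, 0.12/(1 − f)) ≥ 6 − x].

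| Assumed f | Null rate among counted | Type I error, A | Type I error, B | Null futility stop, A | Null futility stop, B |
|---|---|---|---|---|---|
| 0 | 0.120 | 0.094 | 0.094 | 0.60 | 0.60 |
| 2% | 0.122 | 0.101 | 0.100 | 0.58 | 0.60 |
| 5% | 0.126 | 0.113 | 0.110 | 0.56 | 0.60 |
| 10% | 0.133 | 0.137 | 0.130 | 0.53 | 0.60 |
| 20% | 0.150 | 0.204 | 0.176 | 0.44 | 0.60 |

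Under A the error passes 0.10 at f of about 1.7%, and under B at about 2%. One replaced failure per 28 treated is 1/28 = 3.6%.

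**Step 4: replaced failures stay in the analysis set.** If the cut-off remains 6, nothing improves, because successes can come only from the 27 patients not replaced. If the p value is instead recalculated at the attained N, the single-stage value for 6 DCS at p0 = 0.12 is 0.097 at N = 27, 0.111 at N = 28 and 0.143 at N = 30. Six successes then no longer meet 0.10, so the fixed rule and the recalculated test disagree.

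**The case against.** **Replacement may govern accrual only.** No sentence says that replaced patients leave the 19 and 27, and the two treated-patient statements point the other way. This stands as an argument against presenting reading A as the plan. It also means that a lower chance of futility stopping is not established, since under B it stays at 0.60. It does not remove the conflict, because under B the final error still rises.

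**The plan foresees a changed sample size.** The recalculated p value would contain the inflation if replaced patients stay in the denominator. That is fair, but it then contradicts the rule of at least 6 DCS (step 4).

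**The size is unknown.** A reader might take the cited 1.8-month median time to progression, assume exponential times, and infer f of about 30% with a type I error of about 0.30. The article does not support this:

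- The first scheduled scan is at week 8 ± 1 (Study procedures, Table 3 notes), so only clinically evident failure would lead to replacement by week 4.
- The same exponential curve gives 24% progression-free at 16 weeks, twice the 12% null rate.
- Eligibility requires an estimated life expectancy above three months, which argues against many very early deaths.

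**The historical 12% may rest on a different denominator.** The article does not say how the seven earlier trials treated early dropouts, so applying 12% to all dosed patients is an assumption.

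**Details may sit in the full protocol or SAP.** They may, and silence on such details would be no finding. Here, however, the article states a rule that exempts only toxicity and conflicts with its own counting statements.

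**Conclusion.** The point holds as a contradiction to be reconciled, with a conditional effect on the error rate. The replacement sentence covers dosed patients who are already failures on the primary endpoint, and it cannot be squared with the treated-patient counts and the fixed cut-offs.

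If those patients do not occupy places in the 19 and 27, the type I error moves from 0.094 to about 0.10 at f = 2%, 0.11 at 5%, 0.13 to 0.14 at 10% and 0.18 to 0.20 at 20%. The lower value in each range applies when stage 1 counts the first 19 treated. Any higher f is only an upper guide.

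The results rest on an assumed f and on the 12% null rate applying to all dosed patients. The bias runs in one direction, towards calling an inactive drug promising. Replacing patients who leave for reasons unrelated to outcome does not inflate the error. The text therefore does not support a flat statement that the false-positive rate is far above 10%, or that every early withdrawal must be scored as a failure.

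**What to change.** Reword the replacement sentence so that any dosed patient who progresses, deteriorates from disease or dies in the first four weeks is not replaced and counts as DCF in the 19 and in the 27. Name death explicitly. Limit replacement to patients never dosed or who leave for reasons clearly unrelated to outcome. Use this one set for the stage 1 decision, the final decision and the reported disease control rate, and align the at-least-one-dose sentence with it. This is a counting rule and leaves treatment decisions untouched.

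Scoring all early withdrawals as DCF would go too far. Planned power is 0.900 with no slack. If 2%, 5% or 10% of patients left for unrelated reasons and were counted as failures, the success rate of interest would fall to 0.32 × 0.98, 0.32 × 0.95 or 0.32 × 0.90, and power to 0.887, 0.866 or 0.825.

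The cost is a few changed sentences and a slightly less favourable observed disease control rate. The planned 27 does not change, and the planned type I error of 0.094 and power of 0.90 are restored.
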